### Secondary endpoints (variables)

Safety evaluation, as measured by AEs, Adverse Reactions (ARs), SAEs, Serious ARs (SARs):

Frequency and type of adverse reaction will be evaluated during the first 45 days. The responsible doctor will have to answer if the AE is related to the treatment of enzalutamide or if the patient has started any other investigational drug, and state the possible relationship to either drug

**Duration of supplemental oxygen (days):**

Total days of extra oxygen described as any additional oxygen given to the patient at any time during the day between 00-24.

Need of mechanical ventilation:

If the patient is in need of mechanical ventilation the date of this will be defined. Evaluated for 30 days and after 6 months.

**Laboratory assessment:**

The local clinical lab will be used for all laboratory evaluation. Hb, LPK, B-lymphocytes, CRP, IL-6, ASAT, ALAT, ALP, Krea, D-dimer

**Virus load assessment:**

PCR based SARS-CoV-2 measurement from upper respiratory tract.

The tests will be handled in the clinic where the patients is admitted at day 0, 2, 4 and 6. If the patient is discharged before day 6, the last test will be taken at the day of discharge.

Only the relative change of the PCR will compared for the patient and therefore the PCR will be performed at the same day after all sample have been collected at the labs used by the local clinic where the samples has been taken, or transferred to a central study laboratory

**Hospital stay (days)**

Evaluated for 45 days and after 6 months

Any hospitalization any time during any day between 00-24 will be considered as admitted to the hospital that day. At day 2, 4, 6, 7, 14, 21, 30, 45 and 6 months the form includes if the patient is admitted primarily based on COVID-19 symptoms.

**Re-admission to hospital due to rebound COVID-19**

Evaluated for 45 days and after 6 months

Any hospitalization any time during any day between 00-24 will be considered as admitted to the hospital that day. Only if the patient has been home from one day to the next it will be described as re-admission (and at least 12 hours). Any worsening symptoms considered to be a consequence from COVID-19 requiring re-hospitalization is regarded as a rebound event. Rehabilitation at hospital with stable symptoms is not regarded as a rebound event.

**Mortality at 6 months**

Death due to any cause and death date will be found by the study nurse through the medical records or by death registry.

**Hormonal status at 6 months**

The local clinical laboratory will be used to evaluate the hormonal status. FSH, LH, SHBG, testosterone and estrogen/estradiol levels

**Serological immunity for COVID-19 at 6 months**

Serum blood sample will be analyzed centrally for antibodies against Sars-CoV2.

## Methods for measurement of endpoints (variables) for clinical safety

The safety endpoint includes clinical evaluation day 0, 2, 4, 6, 7, 14, 21, 30 and 45. For days 14, 21, 30, and 45 a variation of ± 2 days is allowed. For the 6 months evaluation a variation of ± 2 weeks is allowed. The local routine, and measurement methods available, will be used to evaluate heart rate (per minutes), respiration frequency (per minutes), blood pressure (Systolic blood pressure/diastolic blood pressure), fever (the method will be noted) and saturation (the oxygen supply l/min will be noted).

# Handling of Adverse Events

## Definitions

### Adverse Event (AE)

Adverse Event (AE): Any untoward medical occurrence in a clinical investigation subject administered a medicinal product and, which does not necessarily have a causal relationship with the treatment, can be an unfavorable and unintended sign (including an abnormal laboratory discovery), symptom or disease temporally associated with the use of the medicinal (investigational) product, whether or not related to the medicinal (investigational) product.

### Adverse Reaction (AR)

In the pre-approval clinical experience with a new medicinal product or new use of a medicinal product, and particularly as the therapeutic dose(s) may not be established, all noxious and unintended reactions to the medicinal product related to any dose should be considered an adverse reaction (AR). The phrase “reaction” to a medicinal product means that the causal relationship between the medical product and an adverse event is at least a reasonable possibility; that is the relationship cannot be ruled out.

### Serious Adverse Event (SAE)

Serious adverse event (SAE): Any untoward medical occurrence that at any dose:

- results in death
- is life-threatening
- requires inpatient hospitalization or prolongation of existing hospitalization
- results in persistent or significant disability or incapacity
- results in a congenital anomaly/malformation

Medical and scientific assessment will be made to determine if an event is “serious” and whether it would prompt reporting in other situations, for example important medical events that may not be directly life-threatening or result in death or hospitalization but may compromise the study subject or may require intervention to prevent one of the other results set forth in the definitions above. These should also normally be considered as SAEs.

### Suspected Unexpected Serious Adverse Reaction (SUSAR)

SUSAR: A reaction/event that is unexpected, serious, and suspected to be caused by the treatment, i.e. adverse events that are not included in the SPC.

## Assessment of Adverse Events

### Assessment of causal relationship

The investigator is responsible for determining whether there is a causal relationship between the AE/SAE and use of the investigational product. Further in this trial the assessment will also be taken to define if there is any causal relationship to any investigational therapy in trials starting after the 7 days follow up in this trial (or after end of trial due to other reasons).

Those AEs which are suspected of having a relationship to the investigational product will be followed up until the subject has recovered or is well taken care of and on their way to good recovery (see also section 9.4, Follow-up of Adverse Events).

All AE will be categorized either as likely related, possibly related, or not related, in accordance with the definitions below:

**Likely related**: Clinical event, including abnormal results from laboratory analyses, occurring within a reasonable time after administration of the intervention/investigational product. It is unlikely that the event can be attributed to underlying disease or other medications, but is most likely caused by the investigational product and its emergence is reasonable in relationship with use of the investigational product.

**Possibly related**: Clinical event, including abnormal results from laboratory analyses, occurring within a reasonable time after administration of the intervention/investigational product. The event could be explained by the investigational product and its emergence is reasonable in relationship with use of the investigational product, but there is insufficient information to determine the relationship. The event could be explained by an underlying disease or other medications.

**Not related**: Clinical event, including abnormal results from laboratory analyses, that is not reasonably related to the use of the intervention/investigational product. The event is unlikely related to the intervention/investigational product and can be explained by other medications or underlying disease.

### Assessment of intensity

Each adverse event shall be classified by CTCAEv5.0 criterias. (<https://ctep.cancer.gov/protocolDevelopment/electronic_applications/ctc.htm#ctc_50>).

### Assessment of seriousness

The investigator is responsible for assessing the seriousness (serious or non-serious). If the incident is considered serious, this should be reported as a serious adverse event (SAE) by the investigator to the sponsor. See also section 9.3.1, Reporting of Serious Adverse Events (SAE).

## Reporting and registration of Adverse Events (AE)

From the time of signed informed consent until 45 days, for all patients in the trial, AE will be assessed. All AE that occur during the study and which are observed by the investigator/study nurse or reported by the subject will be registered in the CRF regardless of whether they are related to the investigational product or not. Assessment of causal relationship, severity, and whether the AE is considered to be an SAE or not will be done by the investigator directly in CRF/on study-specific worksheet. A study nurse will fill in information from study-specific worksheet in the eCRF. At minimum, for each AE/SAE, a description of the event is recorded (diagnosis/symptom if diagnosis is missing), start and stop dates, causal relationship, severity, if the AE is considered to be an SAE or not, measures and outcome. Due to the COVID-19 disease local routines will be adopted to secure the personal in the study in the management of the transfer from worksheet to the eCRF.

Events not reported as AE in this trial

The COVID-19 disease has a clinical course including serious illness with potential threat to the patient’s life. These parameters will be followed (see list below) and any change in these parameters will not be reported as AE or SAE.

List of parameters expected:

- Oxygen consumption
- Fever
- Need of mechanical respiratory ventilation
- Dizziness
- Hypertension
- Hypotension
- Tachycardia
- Bradycardia

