### Potential risks for study participants due to enzalutamide treatment

Enzalutamide is a potent androgen receptor inhibitor with effect on many organs including muscles, central nervous system (CNS), reproductive organs and the immune system. Even though enzalutamide is well tolerated and has few serious side effects there is an increased risk of some side effects related mostly to the CNS effects. The trials have been performed in men taking enzalutamide for sometimes many years and in many cases in metastatic prostate cancer.

The reported common side effects in both treated men and women include headache, amnesia, asthenia, tiredness, restless legs, anxiety and hot flushes. The more severe side effects include seizure (the incidence was 0.4% (13 of 3179 men) in the enzalutamide arm compared to 0.1% in the placebo arm of the combination of the trials). In the registration trials there was a small increased risk of ischemic heart disease of 2.5% compared to 1.4% in the placebo arm. The DSUR side effect report to the Swedish Medical product agency (DSUR_31AUG2018), states in the accumulated analysis: “Taken together, the non-clinical and clinical data suggest that enzalutamide is not associated with an increased risk of QT prolongation, ischemic heart disease, heart failure or arrhythmias”.

There are some possible interactions with other drugs due to induction of many cyp-enzymes which has led to exclusion criteria (below) and a notification to the clinics to be aware of and adjust the doses of Azitromycin and omeprazole.

The effect on the desire and potency due to androgen signaling inhibition of enzalutamide is known but is reversible. The effect by enzalutamide on the bone-homeostasis after long time treatment and breast tissue (especially on men) after a couple of months treatment, leading to osteoporosis and gynecomastia, respectively, are unlikely to be seen in the short-term treatment. Interactions of Enzalutamide with other medicinal products are mostly due to liver enzyme induction and may also be of less importance due to the short time of treatment. To minimize this risk we will exclude patients using medicinal products known to interact with the enzalutamide treatment.

For updated SPC see Fass.se (<https://www.fass.se/LIF/product?userType=0&nplId=20160310000078>)

The patients with COVID-19 disease with mild to severe symptoms may experience other side effects compared to the subject previously treated with enzalutamide.

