# Study design and procedures

## Overall study design

This trial is a non-blinded, multicenter, prospective randomized PHASE II clinical trial of enzalutamide treatment to decrease the comorbidity in patients with Corona virus disease 2019 (COVID-19). The trial will be conducted in three phases: explorative phase is to identify any unexpected serious effect of enzalutamide treatment in this novel diagnosis. The second phase (prolongation) will be conducted to receive outcome data to be able to conduct power calculation for the last third phase (full trial). See more details below.

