### Reporting of Serious Adverse Events (SAE)

Serious adverse events (SAE) are reported to the sponsor, via fax to Kliniskt Forskningscentrum Umeå, on a special SAE form within 24 hours of the investigator (or any other study staff) being informed of the SAE. The investigator determines if the event meets the protocol definition of an SAE, assesses causal relationship and intensity of the event. All SAE are reported to the sponsor independent of causality. The sponsor decides if the SAE fulfills the SUSAR criteria, and if so, is responsible for notifying the regulatory authorities (for SUSAR timelines see section 9.3.2).

Follow-up information describing the outcome and handling of the SAE is reported, via fax to Kliniskt Forskningscentrum Umeå, as soon as this information is available. The original should be kept in the Investigator Site File.

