### Secondary objectives

Frequencies of Adverse events will be compared between the two arms using Fisher’s exact test.

Duration of supplemental oxygen (days) will compared between study arms using linear regression adjusted for gender and site.

Time to need of mechanical ventilation will be compared using the ordinal scale, between study arms using Cox regression. And the frequency of need of mechanical ventilation in the two arms will be tested using Fisher’s exact test.

Laboratory assessments at each time of measurement will be compared to baseline and extreme value and differences between study arms evaluated using linear or generalized linear regression adjusting for site, age and gender.

The change in viral load on day 2, 4 and 6 as compared to baseline will be compared between study arms. Also, the maximum decrease in viral load will be calculated, as the difference between observed value and maximal observed value, and compared between study arms. The analyses will be performed using linear regression adjusting for site and gender.

Total hospital stay (days) evaluated at 30 days and 6 months will be compared between groups using linear regression adjusting for site, age and gender.

Frequency of re-admission to hospital due to rebound COVID-19 will be compared between study arms using Fisher’s exact test.

Time to death will be compared between study arms using Cox regression adjusting for site and gender.

Hormonal status at 6 months will be compared to normal reference values and compared between study arms.

Frequency of serological immunity for Covid-19 will be compared between the study arms using Fisher’s exact test.

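### Section 9.3 exempts eight listed parameters from AE and SAE reporting even when the event is serious or suspected to be caused by enzalutamide, which contradicts the protocol's own SAE rules and closes the SUSAR route

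*Protocol*

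**What the plan says.** Section 9.3 (Reporting and registration of Adverse Events) opens with a general rule: "From the time of signed informed consent until 45 days, for all patients in the trial, AE will be assessed", and all AEs are registered whether or not they are related to the product. It then carves out events attributed to the course of COVID-19. The list is oxygen consumption, fever, "Need of mechanical respiratory ventilation", dizziness, hypertension, hypotension, tachycardia and bradycardia. For these, "any change in these parameters will not be reported as AE or SAE". No limit is set by grade, seriousness or suspected relation.

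Other parts of the protocol bear on this:

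- Section 9.3.1: "All SAE are reported to the sponsor independent of causality". The sponsor then decides which of the reported SAEs are SUSARs.
- Overall study design: the "explorative phase is to identify any unexpected serious effect of enzalutamide treatment in this novel diagnosis". The Explorative phase subsection adds that this phase matters for finding serious adverse events related to the drug.
- Potential risks for study participants due to enzalutamide treatment: "there is an increased risk of some side effects related mostly to the CNS effects".
- Section 10.2.1, Secondary objectives: "Frequencies of Adverse events will be compared between the two arms using" Fisher's exact test.

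**The concern.** Events expected in the disease are often exempted from AE reporting, and that is not itself an error. The difficulty is that this exemption has no exit. A life-threatening bradycardia that the investigator considers likely related to enzalutamide is an SAE by definition and must be reported under one section, yet another section says it is not reportable.

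Expectedness is also judged on the wrong scale. Sections 9.1.4 and 9.8 measure it against the product's SPC. Section 9.3 replaces this with what is expected in COVID-19, and does so before any causality assessment. Whether such an event comes from the disease or from the drug is what the explorative phase is meant to find out. The risk section itself says that COVID-19 patients may have side effects different from those of earlier users.

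An exempt event receives no CTCAE grade, no causality or seriousness assessment and no 24-hour report. It is absent from the annual summary of SAEs, from the AE comparison, and from any count of SAEs used to consider premature termination.

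**Working it through.** The protocol states no power or detection figure for adverse events, so there is no figure to reproduce. The check is mainly a comparison of sections.

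**Step 1. Follow one event through the rules.** Take a life-threatening hypotension in an enzalutamide patient, judged possibly related.

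| Section | Treatment of the event |
|---|---|
| 9.1.3 SAE definition | Life-threatening, so an SAE |
| 9.2.3 Seriousness | Investigator reports it to the sponsor |
| 9.3.1 SAE reporting | Within 24 hours, whatever the cause |
| 9.1.4, 9.3.2 SUSAR | Assessed by the sponsor, starting from the reported SAE |
| 9.3 Exemption | Hypotension is listed, so neither AE nor SAE |

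The last row cannot be followed together with the others. If it is followed, the SUSAR step has no input.

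**Step 2. What is captured by another route.**

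| Parameter | Other capture in the protocol | What remains lost |
|---|---|---|
| Mechanical ventilation | Part of a primary endpoint (Cox regression); secondary endpoint with its date recorded (Cox and Fisher) | Case-level causality only |
| Heart rate, blood pressure | Section 8.2: days 0, 2, 4, 6, 7, 14, 21, 30 and 45; section 10.2.1 summarises clinical parameters by arm | Events between evaluations; seriousness and causality |
| Fever, oxygen | Temperature and saturation with oxygen flow in section 8.2; days of oxygen; ordinal scale | Case-level assessment |
| Dizziness | No specific item named in the visible text | Possibly all detail |

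Drug accountability is recorded for days 0 to 4 (section 7.4). Days 1 and 3 of dosing have no scheduled evaluation under section 8.2.

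**Step 3. Why case review matters at this size.** Inputs: 45 patients (Explorative phase) and 2:1 allocation (section 7.5). 45 × 2/3 = 30 on enzalutamide and 45 × 1/3 = 15 controls, approximately.

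- Fisher's exact test, two-sided 0.05 (assumed level), with 0/15 in control: 7/30 gives p = 0.077 and 8/30 gives p = 0.038. The smallest detectable excess is therefore 8/30 = 27% against 0%.
- Chance of at least one event among 30 treated patients = 1 − (1 − p)^30. The rates p are assumptions, not from the documents: 1% gives 26%, 2% gives 46%, 5% gives 79%, 10% gives 96%.

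So at a true rate of 5% to 10%, one or more cases would probably occur but a formal test would probably not flag them. Recognition would depend on someone grading the individual case and judging its cause.

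**Step 4. Check on the remedy.** The trial is open-label and controls take no enzalutamide, so no control event can be suspected to be related to it. Suppose dizziness is equally common, 8/30 and 4/15 (both 27%), and is reported only if suspected to be related. In the extreme case where all 8 are so judged, the AE table shows 8/30 against 0/15, p = 0.038, with no true difference. A relatedness trigger therefore needs protection in the between-arm comparison.

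**The case against.** The strongest defence is that these are disease manifestations already captured elsewhere, and much of that stands.

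- A reader might infer that ventilation events are hidden. They are not: they are among the most closely compared outcomes in the trial. Death is not on the list and remains an SAE.
- A reader might infer that heart-rate and blood-pressure signals vanish. Scheduled values are safety measurements and clinical parameters are summarised by arm, so the loss is partial.
- A reader might infer that dizziness is recorded nowhere. The exempting sentence itself says "These parameters will be followed (see list below"), dizziness is on that list, and the CRF is not shown. Only the absence of a named collection point can be claimed.
- A reader might infer that the list covers known enzalutamide effects. The protocol does not name dizziness or changes in blood pressure or heart rate as drug effects. The side effects it does name, including headache, seizure and ischaemic heart disease, are not exempt. It also quotes a safety report that found no increased risk of arrhythmia.
- A reader might infer that the DSMB sees nothing on these parameters. Its weekly report is mentioned without its content, so this cannot be said either way.

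None of this resolves Step 1. Endpoint data and scheduled vital signs carry no judgement of seriousness, causality or expectedness, and they do not start SUSAR assessment.

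**Conclusion.** The point holds as a contradiction between safety rules with a practical consequence. As written, section 9.3 removes serious and suspected drug-related events in the listed parameters from the route that sections 9.1.3, 9.2.3, 9.3.1 and 9.3.2 require, in both arms and up to day 45. The loss is of events between evaluations and of case-level assessment, not of the whole safety signal. It is clearest for dizziness, where no collection item is named although the protocol describes the drug's side effects as mostly CNS-related.

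The contradiction rests on the text alone and needs no assumed rate. The supporting figures assume an exact 30:15 split and a two-sided 5% level; the 1% to 10% event rates are illustrative. They show why individual cases matter at 45 patients. They do not estimate how many events would be missed. Because an SAE suspected to be related could go unassessed for expectedness, the wording should be corrected rather than left to local interpretation.

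**What to change.** Reconcile section 9.3 with sections 9.1.3, 9.2.3 and 9.3.1:

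1. Limit the exemption to listed events that are non-serious **and** not suspected to be related to enzalutamide. Listed events that meet the SAE definition, or are suspected to be related, follow the ordinary AE, SAE and SUSAR route.
2. Ventilation judged to be due to COVID-19 progression may stay exempt, because it is captured as an endpoint. Without this, nearly every ventilation would also generate an SAE form.
3. Tabulate all eight parameters by arm, irrespective of causality, in the DSMB report and the final safety tables. Add a yes/no item for dizziness at each evaluation.
4. Keep listed events that were reported only because of suspected relatedness out of the between-arm Fisher comparison, or show them separately, for the reason in Step 4 of the working.

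The cost is amended protocol wording, one eCRF item and some extra SAE forms. The number of forms cannot be estimated from the protocol. It will depend partly on how prolonged hospitalisation for oxygen need is handled, so the amended text should say so explicitly.
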